### Data Collection Technique and Tools

A proforma will be developed for data collection. A questionnaire will be prepared; counselors will ask the questions and the information will be recorded in a register. This information will be transferred to an Excel (Microsoft Corp) sheet on a daily basis.

### Plan for Supervision and Monitoring

The study will be carried out by a team of investigators. The principal investigator will provide orientation for the involved staff 1 week prior to participant enrollment. The issues that might arise during the course of data collection will be resolved by mutual discussion between the investigators. The study will be supervised remotely by the Seva team.

### Plan for Data Management and Analysis

Study records that identify the patients will be kept confidential, as required by law. All records pertaining to the patients’ involvement in this research study will be stored in a locked file cabinet in the hospital. A case number will indicate the patients’ identity on these records. This information will only be accessible to the authors.

### Expected Outcome of the Research Results

We expect to determine whether we can defer the 1-week cataract surgery follow-up visit of patients to the hospital.

### Primary Outcome

Visual acuity measurements serve as the most important primary outcome. This includes assessing the level of visual improvement or stability achieved by patients during the 4-week follow-up period. Visual acuity outcomes can provide insights into the effectiveness of deferring follow-up visits for achieving comparable visual outcomes to the standard practice of early postoperative visits.

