Limburg et al [9] investigated the benefits of postoperative follow-up in India and concluded that visual acuity at hospital discharge was not representative of visual acuity several weeks after surgery [10]. However, a study by Congdon et al [11] concluded that early vision assessment of all patients and a follow-up assessment only for patients who return to the clinic without prompting were adequate to ensure the quality of cataract surgical services. This is again countered by a study by Gupta et al [12], who presented evidence of substantial changes between visual acuity on the first postoperative day and at subsequent follow-up. Postoperative complications and uncorrected refractive errors are 2 major issues that lead to poor visual outcomes [5,13-16]. Both issues can be wholly addressed by promoting and ensuring postoperative follow-up at the designated time [17-20]. As per the National Programme of Control of Blindness, Vision 2020: Right to Sight, the recommended postoperative follow‑up visit schedule is a first follow‑up on the first postoperative day by the surgeon (mandatory), a second follow‑up between day 7 and day 10, and a third follow‑up (with refractive correction) between day 30 and day 45 [21]. Saeed et al [22] and Tinley et al [23] concluded that postoperative follow‑up visits can be safely deferred up to 2 weeks after cataract surgery, thereby enhancing the efficiency of day care units. Meltzer et al [24] performed a study using data from the PRECOG (Prospective Review of Early Cataract Outcomes and Grading) trial and reported that visual acuity immediately after cataract surgery was highly correlated with visual acuity after 40 days, suggesting that for the purposes of quality assessment, follow‑up of all patients is not needed. A study by Deshpande et al [25] concluded that visual outcomes after uneventful cataract surgery were comparable between patients followed up on days 3 to 7 and days 25 to 30 in comparison to patients directly followed up on days 25 to 30. Additionally, it was observed that the first follow‑up visit could be safely deferred until 4 weeks after uneventful cataract surgery, including phacoemulsification or small-incision cataract surgery (SICS), in patients with no preexisting ocular or systemic comorbidity [25]. The purpose of this study is to evaluate, from a safety perspective, altering the standard postoperative management guidelines after cataract surgery so that the first follow‑up visit at 1 week is deferred in patients with no significant preexisting ocular or systemic comorbidity and no intraoperative surgical complications or immediate postoperative complications at the time of discharge from the hospital.

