### Specific Objectives

The specific objectives are (1) to compare postoperative visual outcomes after a day 0 examination in patients with either 2 follow‑up visits, one on day 7 and the other on day 30, or 1 ophthalmic follow‑up visit between day 25 and day 30; (2) to assess the safety of deferring the first follow‑up visit at 1 week; and (3) to perform a cost-benefit analysis of the intervention.

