## Methods

### Study Design, Setting, and Participants

This will be a prospective, quantitative, experimental, noninferiority control study of health services use. Selected patients undergoing cataract surgery at Reiyukai Eiko Masunaga Eye Hospital irrespective of the type of surgery (SICS or phacoemulsification) will be included in the study.

All enrolled patients will undergo an examination on the first postoperative day conducted by an ophthalmologist who is unaware of the patient’s group assignment. Subsequently, the patient will proceed to the counselor’s office, where a unique identification number will be generated and the patient will be randomized into either group 1 or group 2.

In group 1, patients will be instructed to attend follow-up visits at 1 week and 1 month postoperatively. In group 2, patients will be instructed to attend a follow-up visit at 1 month postoperatively only. During the visit, the patients will receive detailed guidance on the appropriate use of medications and be educated about the signs and symptoms they should be vigilant for. The specific date of the postoperative visit will also be communicated.

At each follow-up visit, the patient will directly visit the counselor’s office. Upon arrival, they will be provided with a blank sheet of paper containing the unique identification number assigned to them on the first postoperative day. Visual acuity testing will be conducted by a blinded optometrist, while slit lamp biomicroscopy will be performed by a blinded ophthalmologist. Before leaving the hospital, the patient will return the paper to the counselor, who will then enter the necessary information into the patient’s file. 

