### Exclusion Criteria

Patients will be excluded if (1) there are complications during the surgery that warrant more frequent follow-up visits (eg, premature entry, posterior capsular rupture, zonular dialysis, postoperative hyphema, toxic anterior segment syndrome, or postoperative fibrin in the anterior chamber); (2) the surgery is for complicated cataract, traumatic cataract, ocular hypertension, or if the patient has drug allergies; (3) the patients has a history of diseases that might affect postoperative visual outcomes, such as uveitis, glaucoma, viral keratitis, corneal scarring, hypertensive retinopathy, diabetic retinopathy, central retinal vein occlusion, branched retinal vein occlusion, or age-related macular degeneration; (4) the patient is unwilling to participate or does not provide written consent; and (5) the patient misses the follow-up visits.

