### Sample Size and Sampling Technique

Sample size is calculated as follows: 2[Zα + Z1 – β] 2 × (sd2/d2) = 2 [1.96 + 1.645 ] 2 × [(0.1125)2/(0.025)2] = 263 for one group, where reference mean values for postoperative visual outcomes are taken from the study conducted by Deshpande et al [25]. The number of participants in intervention group will be 263 and the number of participants in the control (reference) group will be 263. We will use a random sampling technique and computer-generated random numbers to assign patients to the intervention or control group. We generated randomized numbers with a commonly used method [26]. The assignment will be done by the counsellor on the first postoperative day. The researchers will be masked as to randomization at all postoperative visits.

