### Limitations and Challenges

There are potential challenges associated with deferring postoperative follow-up visits. It is important to carefully consider the selection criteria for eligible patients to ensure that only those with a low risk of complications are included in the study. Additionally, proper communication channels must be established to ensure patients have access to health care providers in case of emergency concerns or complications during the extended follow-up period.

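### Safe deferral would rest on P>.05 for visual acuity, a comparison that can miss a small excess of poor results; the planned complication comparison has no role in the conclusion

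*Protocol article*

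**What the plan says.** All references are to the protocol article.

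- **Purpose.** Background gives the aim as "to evaluate, from a safety perspective, altering the standard postoperative management guidelines after cataract surgery". Specific Objectives lists safety of deferral second, and the Abstract's Conclusions section hopes to conclude that deferral is safe.
- **Design.** Study Design, Setting, and Participants calls the trial a "noninferiority control study of health services use". It provides for blinded acuity testing and blinded slit-lamp examination at follow-up.
- **Population.** Surgery must be uncomplicated, and listed eye diseases are excluded. Limitations and Challenges wants to ensure that "only those with a low risk of complications are included in the study".
- **Primary outcome.** "Visual acuity measurements serve as the most important primary outcome". The section mentions improvement or stability but names no summary measure and no threshold for a poor result.
- **Sizing.** The calculation uses SD 0.1125 and d 0.025, and "reference mean values for postoperative visual outcomes are taken from the study" cited there. The acuity scale is not stated.
- **Other outcomes.** The only named secondary outcome is the cost analysis.
- **Inference.** The Results section infers comparability from the absence of a significant difference in acuity (P>.05). The Abstract mentions a minimum clinically important difference but gives no value. The Results section also says that numbers of patients with postoperative complications will be compared between groups, without saying how the comparison bears on the conclusion.

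**The concern.** Omitting the 1-week check can harm only patients who would have had something to find at that visit. Eligibility makes them few, which is sensible but means that any harm is concentrated in a small share of patients. In a comparison of means, those patients are averaged with a large majority whose result does not depend on the schedule. A non-significant difference is then compatible with an excess of poor results under deferral.

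The complication comparison is the natural safety evidence, but it is neither a named outcome nor part of the stated inference. Followed as written, the plan allows a conclusion of safe deferral from P>.05 on acuity, whatever the complication counts or the number of eyes with poor final vision.

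**Working it through.** **Inputs from the article (Sample Size and Sampling Technique; Results):** SD 0.1125, d 0.025, multipliers 1.96 and 1.645, 263 per group, comparability if P>.05.

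**Assumptions, not in the article:** the scale is logMAR; a share f of the deferred group loses an amount L; nobody in the control group does; acuity is otherwise normal with the stated SD; the comparison is of means.

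**1. The plan's own figure.** 2 × (1.96 + 1.645)² × (0.1125/0.025)² = 526.3 per group. The stated 263 appears only without the leading 2: (3.605)² × (4.5)² = 263.2. This is a separate defect. The planned 263 is used below.

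**2. Precision.** SE of the difference = 0.1125 × √(2/263) = 0.0098. With no extra spread, P<.05 needs an observed difference of about 1.96 × 0.0098 = 0.019.

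**3. Mean shift = f × L.**
- 2% losing 0.5 (about 5 of 263): 0.02 × 0.5 = 0.010
- 3% losing 0.5 (about 8 of 263): 0.03 × 0.5 = 0.015
- To reach d = 0.025 at L = 0.5: 0.025/0.5 = 5%, about 13 of 263

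**4. Chance of P>.05.** The harmed patients also widen the spread in the deferred group: SD = √(0.1125² + f(1−f)L²). For f = 3%, L = 0.5 this is 0.1412, so SE = √((0.1125² + 0.1412²)/263) = 0.0111. The shift is then 0.015/0.0111 = 1.35 standard errors, and the chance of P>.05 is about Φ(1.96 − 1.35) = 0.73. Simulation of 3,000 trials per setting with a Welch test agrees (0.745):

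| Share harmed | Loss | Mean shift | P>.05 | Upper 95% limit below 0.025 |
|---|---|---|---|---|
| 2% | 0.3 | 0.006 | 91% | 46% |
| 2% | 0.5 | 0.010 | 86% | 29% |
| 3% | 0.5 | 0.015 | 75% | 16% |
| 3% | 0.8 | 0.024 | 54% | 4% |
| 5% | 0.3 | 0.015 | 71% | 17% |
| 5% | 0.5 | 0.025 | 45% | 3% |
| 5% | 0.8 | 0.040 | 19% | 0.1% |
| 5% | 1.0 | 0.050 | 11% | 0.1% |

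The last column shows what a noninferiority rule against 0.025 would do with the same data. With 526 per group, 3% losing 0.5 still gives P>.05 in 52% of trials.

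**5. What a proportion would show.** With 3 vs 3 events of 263, the Wilson limits for each group are 0.39% and 3.30% around 1.14%. The Newcombe upper limit for the difference is √((3.30 − 1.14)² + (1.14 − 0.39)²) = 2.3 percentage points. With 8 vs 1 events, the difference is 2.7 points (95% interval about 0.4 to 5.5).

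**The case against.** **Safety is not left to acuity alone.** Complications are to be compared between groups, and a blinded ophthalmologist examines the eye at follow-up. This stands: a reader might infer that average acuity is the trial's only safety evidence, and the article does not support that. What remains is that the comparison is not a named outcome and does not enter the stated inference. It also counts complications, not poor final vision.

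**Low-risk enrolment is no defect.** This stands in full. It is the declared population, and the intended conclusion is limited to uncomplicated surgery. It matters here only because it makes events rare.

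**The mean is inferred.** This also stands. The Primary Outcome section names no summary measure, so the mean is read from the sizing. A rank test would not help: in simulation (300 trials per setting), P>.05 occurred in about 80% to 85% of trials even with 5% harmed. An acuity cut-off might also sit in a fuller plan that is not shown. But the inference rule is fixed in the article, and it gives neither a cut-off nor the complication counts a role.

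**The masking can be overstated.** It might be inferred that serious loss in several percent of patients would generally go unseen. The table does not support that for 5% losing 0.8 or more. Much of the masking comes from the P>.05 rule, and some from the smaller sample size; an interval rule against 0.025 would pass far fewer of these cases.

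**A proportion has little power.** True: on assumed rates of 3% vs 1%, power at 263 per group is about 37% (25% with Fisher's test). The remedy therefore asks for an interval, not a significance test.

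**Conclusion.** The point holds in a limited form. The stated inference, P>.05 on acuity, cannot by itself support a claim of safe deferral, and the complication comparison that could support it has no role in the conclusion. With 2% to 3% of deferred patients losing 0.5, P>.05 would occur in about 75% to 85% of trials at 263 per group. These figures rest on assumed shares and losses, the logMAR reading, no such losses in the control group, and a comparison of means. Part of the effect belongs to the P>.05 rule itself, and the largest harms considered would usually be detected. This is a change that should be made; it does not invalidate the design.

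**What to change.** Keep visual acuity as the primary comparison. Name two key safety outcomes:

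1. the between-group comparison of patients with postoperative complications that the Results section already plans;
2. the proportion in each randomised group with poor final acuity, using one cut-off on the Snellen chart fixed before the data are seen.

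Report each as a risk difference (deferred minus standard) with its 95% confidence interval. Base the statement about safe deferral on the upper limits of those intervals, not on P>.05 for acuity. State in advance how large an upper limit would still be acceptable; that value is for the sponsor to justify.

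Because the Exclusion Criteria remove a participant if "the patient misses the follow-up visits", also report by randomised group how many have no final acuity, so that harmed patients do not drop out of the count unseen.

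The cost is wording and two short analyses of data already to be collected, with no change to the sample size. The downside is wide intervals for rare events: equal counts of 3 and 3 would still leave an excess of about 2.3 percentage points possible. The safety claim becomes more modest.

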### Secondary Outcome

The results of the cost-benefit analysis can be considered a secondary outcome. Conducting a cost-effectiveness analysis allows for the assessment of the economic implications and potential cost savings associated with deferring postoperative follow-up visits. This outcome provides insights into the financial feasibility and efficiency of implementing the deferred follow-up strategy.

We will perform a cost-benefit analysis to compare the economic status of the intervention group and active control group. For this we have to collect financial data on direct and indirect costs. Data on direct costs will be retrieved from the hospital record system, because this is the money paid directly by patients for their treatment after the surgery is recorded, including payments for consultation, medicine, and investigation (if required) at each follow-up visit.

Data on indirect costs, that is, costs incurred to the patient in the process of coming to the follow-up visit, include the following: (1) lost productivity costs (how much money the patient could have earned if the patient hadn’t come to the hospital follow-up visit), (2) transportation costs (the cost incurred while travelling), and (3) companion costs (patients will definitely have a companion, for whom we also have to calculate both costs above (lost productivity and transportation). Data on indirect costs will be obtained from interviews with the patients. We will calculate the average cost per visit, which will ultimately reveal the costs and benefits of the new approach, because the suggested new regimen will eliminate one follow-up visit.

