**Results:**

The study is expected to be completed within 6 to 8 months from the start of the project. Data analysis and report writing will be carried out in a 2-month period. Best-corrected visual acuity will be compared between the 2 groups to determine if the MCID is achieved. The cost-effectiveness of the new approach will also be analyzed.

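### The economic secondary outcome carries two different names, while the only calculation fixed for it, average patient cost per visit, is neither analysis and does not estimate the cost difference between arms

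*Protocol article*

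**What the plan says.** The third of the Specific Objectives is "to perform a cost-benefit analysis of the intervention". The Abstract's Results paragraph instead promises: "The cost-effectiveness of the new approach will also be analyzed".

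Secondary Outcome uses both names. It opens with "The results of the cost-benefit analysis can be considered a secondary outcome", continues with "Conducting a cost-effectiveness analysis allows for the assessment of the economic implications and potential cost savings associated with deferring postoperative follow-up visits", and in its next paragraph returns to the first name: "We will perform a cost-benefit analysis to compare the economic status of the intervention group and active control group".

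Two kinds of cost are collected. Direct costs come from the hospital record system and are payments by patients ("this is the money paid directly by patients for their treatment after the surgery is recorded"). Indirect costs come from patient interviews and cover lost earnings and travel for the patient and a companion. The calculation is then fixed: "We will calculate the average cost per visit, which will ultimately reveal the costs and benefits of the new approach". The reason given is "because the suggested new regimen will eliminate one follow-up visit". The same section says the outcome will inform whether implementing deferral is financially feasible and efficient.

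**The concern.** Cost-effectiveness and cost-benefit are different quantities. The first sets an incremental cost against a difference in effect. The second expresses effects in money and reports a net benefit. With both names on one outcome, a reader cannot tell which result the trial commits to report.

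The calculation that is fixed matches neither name. A per-visit average also removes the feature in which the arms are designed to differ, the number of visits, so the saving comes from the schedule and not from the data. The Discussion (Expected Findings) says patients should be taught warning signs so that they can come to the hospital when needed. Extra visits are therefore foreseen, and they could offset the saving. If more of them occur in the deferred arm, a saving read from the schedule is too large.

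At stake is the result of the only outcome listed under the Secondary Outcome heading, together with an economic promise made in the Abstract.

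**Working it through.** The document states no cost, cost SD or economic target, so there is no figure of the plan's own to reproduce. The check sets the text side by side and then uses arithmetic on assumed values.

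**1. Names**

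| Place | Name used |
|---|---|
| Abstract, Results | cost-effectiveness |
| Specific Objectives, item 3 | cost-benefit |
| Secondary Outcome, first sentence | cost-benefit |
| Secondary Outcome, second sentence | cost-effectiveness |
| Secondary Outcome, second paragraph | cost-benefit, as a comparison of the groups |
| Secondary Outcome, last sentence | average cost per visit |

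**2. What each analysis requires**

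- Cost-effectiveness: the difference in mean cost between arms, set against the difference in effect.
- Cost-benefit: the money value of the difference in effect, minus the difference in mean cost.
- Average cost per visit: total cost divided by number of visits. It contains no effect, no money value for an effect, and no between-arm difference in cost per patient.

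**3. Does cost per visit measure the difference between regimens?**

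Assumptions, none from the document: a scheduled visit costs 1 unit; group 2 has u unscheduled visits per patient in excess of group 1; each unscheduled visit costs k units. From the design, group 1 has 2 scheduled visits after day 1 and group 2 has 1.

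- Cost per patient: group 1 = 2; group 2 = 1 + u·k.
- Saving per patient = 2 − (1 + u·k) = 1 − u·k.
- Cost per visit: group 1 = 2/2 = 1; group 2 = (1 + u·k)/(1 + u).

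| k | u | Cost per patient, group 1 vs group 2 | Saving per patient | Cost per visit, group 1 vs group 2 |
|---|---|---|---|---|
| 1 | 0 | 2.0 vs 1.0 | 1.0 | 1.0 vs 1.0 |
| 1 | 0.5 | 2.0 vs 1.5 | 0.5 | 1.0 vs 1.0 |
| 1 | 1.0 | 2.0 vs 2.0 | 0 | 1.0 vs 1.0 |
| 3 | 0.1 | 2.0 vs 1.3 | 0.7 | 1.0 vs 1.182 |
| 3 | 0.3 | 2.0 vs 1.9 | 0.1 | 1.0 vs 1.462 |
| 3 | 0.5 | 2.0 vs 2.5 | −0.5 | 1.0 vs 1.667 |

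When all visits cost the same (k = 1), cost per visit is 1.0 in both arms whatever the saving. When unscheduled visits cost more (k = 3), a comparison of cost per visit can point the wrong way: at u = 0.1 group 2 is cheaper per patient (1.3 vs 2.0) but dearer per visit (1.182 vs 1.0). The saving disappears at u = 1/k, which is 1 extra visit per patient for k = 1 and about 0.33 for k = 3. Reading the saving from the schedule sets u = 0.

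**4. Perspective**

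Every listed cost falls on the patient or companion, and no hospital cost is listed. Consultation fees are an expense to patients but a receipt to the hospital. These inputs can describe patients' savings. They cannot show whether the hospital can run the strategy affordably or efficiently.

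**The case against.** The strongest defence has four parts.

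*The data are adequate.* Visual acuity is the primary outcome and patient costs are collected at follow-up visits. A reader might infer from the mismatch that a cost-effectiveness result is unobtainable. The documents do not support that: both a cost difference and an effect difference could be formed. The section also plans a comparison between groups, and total cost per patient could be built from the planned records. This stands, and it locates the fault in the names, the fixed summary and the claim, not in the data collection.

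*No ratio is planned.* A reader might go on to argue that cost per unit of acuity would be unstable in a noninferiority trial, where the expected effect difference is near zero. The document specifies no such ratio, so that argument does not measure an error in this plan.

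*The economic conclusion is modest.* The Abstract's Conclusions speak of lower patient expenses and hospital load, and the feasibility sentence promises only insight. It would be too strong to say that no economic statement is supported. Average cost per visit gives a rough patient saving if no unscheduled visit replaces the one removed. That condition is assumed, and the Discussion gives reason to doubt it.

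*An article condenses.* Costing methods and the valuation of effects are commonly left to a fuller document, so their absence is no fault. The conflicting names, the per-visit calculation and the feasibility claim, however, are printed here.

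**Conclusion.** The concern holds as a stated inconsistency with a poorly chosen summary measure. One outcome has two names, and the calculation fixed for it is neither. That calculation does not estimate the between-arm difference, takes its saving from the schedule, leaves out unscheduled visits, and cannot carry a claim about the hospital's finances.

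The size cannot be computed from the document. Under the assumed values, the per-patient saving ranges from the full cost of one visit down to nothing with no change in cost per visit, and it turns negative at 0.5 extra visits per patient if each costs three times a scheduled visit. The illustration rests on u and k, for which the document gives no values; the label conflict and the perspective mismatch do not depend on it.

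The primary acuity comparison is not affected. Nor is this the only further result the article describes: complications and satisfaction appear in its Results section, though not under the Secondary Outcome heading. The correction should be made because this outcome is a specific objective and is promised in the Abstract.

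**What to change.** - Use one label in the Abstract, Specific Objectives and Secondary Outcome: a patient-perspective cost comparison between arms.
- Replace average cost per visit with mean total patient and companion cost per randomised patient over follow-up, counting unscheduled as well as scheduled visits. Report the between-arm difference with a confidence interval.
- State that a saving counts in favour of deferral only alongside the acuity noninferiority result.
- Limit the feasibility and efficiency statement in Secondary Outcome to patients.

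This does not rule out a cost-effectiveness analysis. If the investigators want one, it should be defined as such and kept separate from this outcome.

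The cost is mostly wording. Unscheduled visits must be captured in the hospital records and patient interviews and costs summed by patient, which is slightly more data handling. The economic claim becomes narrower than the one now promised.

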## Discussion

### Expected Findings

The proposed study will investigate the feasibility and potential benefits of deferring postoperative follow-up visits up to 4 weeks after uneventful cataract surgery in a tertiary level eye hospital in Kavrepalanchok.

Deferring postoperative follow-up visits will allow patients to recover in the familiar environment of their homes, reducing the need for immediate travel and associated costs. This can have a positive impact on patient satisfaction and comfort during the recovery period. By avoiding unnecessary trips to the hospital, patients may experience reduced anxiety and stress, leading to an improved overall experience.

By spacing out follow-up visits, health care providers can optimize resource allocation within the tertiary level eye hospital. This approach will allow health care personnel to allocate their time and expertise more efficiently, focusing on patients who require immediate attention or complex postoperative care. Moreover, it can potentially reduce the burden on health care facilities, as fewer appointments are scheduled during the early postoperative period.

Deferring follow-up visits may also improve access to care, particularly for patients residing in remote areas. Traveling to health care facilities shortly after surgery can be challenging, especially for individuals with limited mobility or limited access to transportation. By extending the follow-up period, patients from distant locations can receive necessary care without the immediate need for travel, increasing the likelihood of their adherence to follow-up appointments.

One major concern related to deferring follow-up visits is the potential delay in detecting postoperative complications. Early postoperative visits allow health care providers to closely monitor patients for any signs of infection, inflammation, or other adverse events. When extending the follow-up period, it is crucial to educate patients regarding the signs and symptoms of postoperative complications so that they can visit the hospital, if required, on time. Patients should receive comprehensive information about self-care, potential warning signs, and instructions on when to seek medical attention. This will empower patients to actively participate in their own recovery and promote a sense of responsibility for their eye health.

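### Eye care and medicines bought outside this hospital count as zero cost in both arms, so the saving from deferral will be overstated if deferred patients buy more of them

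*Protocol article*

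**What the plan says.** All the cost rules stand in the protocol article under Secondary Outcome.

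- Direct costs: "Data on direct costs will be retrieved from the hospital record system". The items are patient payments, "including payments for consultation, medicine, and investigation (if required) at each follow-up visit". No other source is named for direct costs.
- Indirect costs: "Data on indirect costs will be obtained from interviews with the patients". They are defined as "costs incurred to the patient in the process of coming to the follow-up visit" and cover lost earnings, transport and the same two items for a companion.
- Purpose: to "compare the economic status of the intervention group and active control group".
- Derivation of the result: "We will calculate the average cost per visit, which will ultimately reveal the costs and benefits of the new approach", and the reason given is "because the suggested new regimen will eliminate one follow-up visit".

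Under Study Design, Setting, and Participants, group 1 is told to attend at 1 week and 1 month, and group 2 at 1 month only. The Abstract places the group 2 visit between days 25 and 30.

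**The concern.** The two cost definitions leave a gap. A payment to a pharmacy, clinic or other hospital is not in this hospital's records. It is also not a cost of travelling to a follow-up visit here, so neither source picks it up.

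The gap might matter for the comparison because the trial removes a scheduled contact from one arm only. A group 1 patient with a worry has a planned visit at day 7, where any payment is recorded. A group 2 patient has no planned visit for about four weeks. If some of those patients buy care nearer home, the plan would report care that moved elsewhere as care that was avoided. The article's Abstract already aims to conclude that patient expenses fall, so the cost result would be used directly to support the new schedule.

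There is a second weakness in the same section. The saving is inferred from an average cost per visit and one removed visit. Under that rule even extra care that is recorded, such as an unscheduled return to this hospital, need not reduce the saving.

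**Working it through.** The article states no cost, no saving and no rate of outside care, so there is no figure to reproduce. The check asks what the stated rule gives and what it leaves out.

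**Inputs from the article.** After day 1, group 1 has two scheduled visits and group 2 has one (Study Design, Setting, and Participants). The result is based on the average cost per visit, here called C (Secondary Outcome).

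**Assumptions, not in the article.**
- p1 and p2 are the shares of control and deferred patients who buy outside care once.
- r is the cost of that purchase in units of C, taken as equal in both arms.
- u1 and u2 are mean unscheduled visits to this hospital per patient, each costing C.

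**Cost per patient after day 1, in units of C.**
- Group 1: 2 + u1 + p1 × r
- Group 2: 1 + u2 + p2 × r
- True saving: 1 − (u2 − u1) − (p2 − p1) × r
- Saving by the stated rule: 1 × 1 = 1

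The rule matches the true saving only when both bracketed differences are zero or cancel. Better cost data alone do not change the 1; the comparison of totals has to change as well.

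**Outside care alone (u1 = u2).** True saving T = 1 − (p2 − p1) × r, and the error as a share of the true saving is 1/T − 1.

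| p2 | p1 | r = 0.5 | r = 1 | r = 2 |
|---|---|---|---|---|
| 5% | 5% | 0% | 0% | 0% |
| 10% | 5% | +2.6% | +5.3% | +11.1% |
| 20% | 5% | +8.1% | +17.6% | +42.9% |
| 30% | 10% | +11.1% | +25.0% | +66.7% |
| 5% | 10% | −2.4% | −4.8% | −9.1% |

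Worked example: p2 = 20%, p1 = 5%, r = 1 gives T = 1 − 0.15 = 0.85, and 1/0.85 − 1 = 17.6%.

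**Extremes.** With p2 = 30%, p1 = 10%, r = 2, T = 1 − 0.40 = 0.60. With p2 = 5%, p1 = 10%, r = 2, T = 1 + 0.10 = 1.10. In every row the true saving stays above zero. At r = 2 it would take a difference of 50 percentage points (1/2) to cancel it.

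**The case against.** **The omission applies to both arms.** This stands. A reader might infer that the saving is certainly overstated, or that the comparison is biased towards deferral. The article does not support that: the direction depends on a between-arm difference in outside spending that it does not give.

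**The documented route for a worried patient leads back to this hospital.** This stands in part. Expected Findings wants patients taught the warning signs so that they return in time if needed. Its remark that "patients from distant locations can receive necessary care without the immediate need for travel" is about access and travel, not about buying care locally. More outside care in group 2 is therefore plausible but is a conjecture. Nothing in the plan would record it if it happened, and the stated rule need not count even the unscheduled returns.

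**The article is condensed.** Data Collection Technique and Tools mentions a questionnaire whose content is not described, and it might ask about outside care. That weakens the point without removing it. Secondary Outcome expressly assigns direct costs to hospital records, so such answers would have no stated place in the analysis.

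**A comparison of arms is already intended.** The section does announce one, but the only method it then gives is average cost per visit with one visit removed. That fixes the saving by design instead of measuring it.

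**Complications.** A reader might also infer that complications treated elsewhere will be missed for the same reason. That does not follow: the payment records are a cost source, and the Results section compares complications over the four weeks without tying them to those records.

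**Conclusion.** The point holds in conditional form. As written, outside eye care and medicines count as zero in both arms, and the saving will be overstated if deferred patients buy more of them than controls. Equal use gives no bias; more use by controls gives an understatement.

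The size cannot be estimated from the article. The span of about −9% to +67% of the true saving rests wholly on assumed shares of 5% to 30% and assumed prices of 0.5 to 2 visit-costs, with equal prices in the two arms and equal unscheduled visits. The upper end needs both a large difference and a high price; a difference of 5 percentage points at one visit-cost gives about 5%. None of these scenarios reverses the sign of the saving, so what is at risk is its reported size.

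This concerns a secondary outcome. It is still worth acting on before enrolment, because the information is cheap to collect at the last visit and hard to recover later.

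**What to change.** 1. In the interview already planned for indirect costs, at the last visit, ask both groups the same scripted questions: since day 1, was any eye care or eye medicine obtained elsewhere; where, when and for what problem; and how much was paid, including travel and companion.
2. Add these amounts to that patient's direct and indirect costs.
3. Replace the inference from average cost per visit with a comparison of mean total cost per patient between the assigned groups, from day 1 to the last visit. Count unscheduled visits to this hospital as well as scheduled ones. Steps 1 and 2 have no effect on the result without this step.
4. Use complications reported in these answers as a supplementary source for the between-group complication comparison described in the Results section.

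The price is a few extra questions and possibly a smaller reported saving. Recall over about four weeks will be imperfect, and the error may differ between arms: counselors both assign the groups and ask the questionnaire, and group 1 has a day-7 visit to anchor memory. Fixed wording limits this but does not remove it. The questions also cannot reach patients who miss the last visit, whom the Exclusion Criteria remove.
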